### Statistical analysis

2.5

All data are recorded into the Microsoft Excel 2010, and then they are analyzed via applying the IBM SPSS Statistics for Windows, version 20 (IBM Corp., Armonk, NY, USA). Afterwards, all the data are expressed with appropriate characteristics such as mean, median, standard deviation as well as percentage. Continuous and categorical variables are analyzed using χ^2^-tests and independent *t* tests, respectively. Intention-to-treat analysis is used for the outcome assessments. When *P* value <.05, it is considered to be significant in statistics.

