### Population and randomization

2.2

100 participants who undergo PELD will be analyzed. In the random envelope, all patients are assigned a random number via using the random number (Table 1), and the result of allocation are hidden. Patients will be randomly divided into bilateral IFB group (with 50 patients) and local infiltration analgesia group (with 50 patients). Inclusion criteria contains

1.patients diagnosed with LDH undergoing PELD;2.people between the ages of 18 and 75;3.consistent imaging evidence of herniation at a same level (CT or MRI);4.receive conservative treatment for 2 months.

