### Outcome measures

2.4

Primary outcomes are pain score at different time point. Visual analog scale (VAS) is used to assess the pain (10: the maximum possible pain and 0: absent pain).^[11]^ The secondary outcomes are the operative time, radiation exposure time, length of hospital stay, and postoperative complications. The radiation exposure time is obtained from the G-arm computer at the end of each procedure. Oswestry Disability Index (ODI)^[12]^ is also recorded at 7 days, 12 weeks, and 1 year postoperatively.

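### The statistical analysis section transposes its two tests, so the VAS primary outcome and the other numeric outcomes are assigned a χ² test that is unsuitable and has little power

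*Protocol article*

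**What the plan says.** Section 2.5 (Statistical analysis) states: "Continuous and categorical variables are analyzed using χ^2^-tests and independent *t* tests, respectively". It adds a significance rule, "When *P* value <.05, it is considered to be significant in statistics", and an analysis set, "Intention-to-treat analysis is used for the outcome assessments". It also says that data will be summarised by means, medians, standard deviations and percentages. No other part of the article, including the abstract, names a test.

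Section 2.4 (Outcome measures) defines what the rule applies to:
- Primary: "Primary outcomes are pain score at different time point". The scale is given as "Visual analog scale (VAS) is used to assess the pain (10: the maximum possible pain and 0: absent pain".
- Secondary: "The secondary outcomes are the operative time, radiation exposure time, length of hospital stay, and postoperative complications".
- ODI, which "is also recorded at 7 days, 12 weeks, and 1 year postoperatively".

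Section 2.2 plans 100 patients, 50 per arm.

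**The concern.** Read literally, section 2.5 cross-tabulates pain scores, times, length of stay and ODI by arm and applies χ², and applies a t test to complications. This is the reverse of the usual pairing.

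A χ² test treats each distinct value as an unordered label. A shift from 6 to 5 counts no differently from a shift from 6 to 0, and a difference in favour of either arm looks the same. The test therefore does not address whether mean pain is lower with the bilateral block, which is the trial's question. What is at stake is the chance of detecting a real effect on the primary outcome. There is also a risk that the test actually used is chosen by undocumented judgement, because the published rule cannot sensibly be followed.

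**Working it through.** The article gives no power, effect size or SD, so it has no figure to reproduce. The check has two parts: matching the rule to the outcomes, and measuring the consequence.

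**1. Rule against outcomes**

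| Outcome (section 2.4) | Type | Test under section 2.5 as written |
|---|---|---|
| VAS pain, several time points (primary) | numeric, 0 to 10 | χ² |
| Operative time | numeric | χ² |
| Radiation exposure time | numeric | χ² |
| Length of stay | numeric | χ² |
| ODI at 7 days, 12 weeks, 1 year | numeric | χ² |
| Postoperative complications | categorical | independent t test |

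**2. Limiting case: all values distinct**

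Suppose 100 patients, 50 per arm, have 100 different values, as could nearly happen for a finely recorded time. The table is 2 × 100, with one patient per column and an expected count of 0.5 in every cell. Each column contributes (1 − 0.5)²/0.5 + (0 − 0.5)²/0.5 = 0.5 + 0.5 = 1. Hence χ² = 100 on 99 df, p = 0.453, whatever the treatment effect.

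**3. VAS primary**

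From the document: 50 per arm, threshold 0.05 (taken as two-sided; the article does not say). Assumed, because the article does not give them: normal scores limited to 0–10, control mean 5, SD 1.5 or 2.0, true difference 0 or 1 point, recorded in whole points or to 0.1. There were 3,000 simulated trials per setting, with Pearson χ² on the distinct values.

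| SD | Recording | χ², no difference | t, no difference | χ² power, 1 point | t power, 1 point |
|---|---|---|---|---|---|
| 1.5 | whole points | 0.028 | 0.045 | 0.52 | 0.91 |
| 1.5 | 0.1 | 0.002 | 0.047 | 0.018 | 0.92 |
| 2.0 | whole points | 0.037 | 0.056 | 0.24 | 0.69 |
| 2.0 | 0.1 | 0.002 | 0.051 | 0.005 | 0.69 |

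Cross-check of the t test by normal approximation, power = Φ(δ/(σ√(2/n)) − 1.96):
- SD 1.5: standard error 1.5 × √(2/50) = 0.30; Φ(3.33 − 1.96) = 0.915.
- SD 2.0: standard error 2.0 × √(2/50) = 0.40; Φ(2.50 − 1.96) = 0.705.

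Both agree with the simulation. The finer the recording, the closer χ² comes to the limiting case in step 2.

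**4. Complications as a yes/no outcome**

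For 0/1 data with N = 100, the pooled t statistic and the uncorrected χ² are linked by χ² = 100t²/(t² + 98). The 5% χ² cut-off of 3.841 corresponds to t² = 98 × 3.841/(100 − 3.841) = 3.915, so |t| = 1.98. This is essentially the 5% cut-off of the t test itself. In simulation (10,000 trials per setting, assumed rates 5% to 30%), the two tests reached the same decision in 99% to 100% of trials. With equal rates the t test rejected in 0.041 to 0.052 of them. For an unordered complication variable with more than two categories a t test would have no meaning, but section 2.4 does not define one.

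**The case against.** The strongest reply is that this is a harmless transposition. Both usual tests are named and only their order is reversed. The same section plans means, standard deviations and percentages, which fit the usual pairing, and an analyst is unlikely to cross-tabulate operative time by patient. This stands as to cause: it is probably a slip. It does not remove the point. The sentence is complete and unambiguous, it is the only test rule shown, and it covers the primary outcome. Nor does an analysis plan that is not shown settle it. The problem is a rule stated wrongly, not detail left out, and a plan with the usual pairing would contradict the published protocol.

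A reader might also go further and infer that every planned comparison is invalid, that no valid p value results, or that no treatment effect could be estimated. The document does not support these readings:
- With no true difference, χ² on VAS rejected in 0.002 to 0.037 of simulated trials. It is conservative, so the failure is lost power and an ill-suited hypothesis, not excess false positives.
- A t test on yes/no complications is practically equivalent to χ².
- Section 2.5 plans means and standard deviations. If these are reported by arm, a crude difference is available whichever test is named. What the stated test lacks is inference on that difference.

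The size of the power loss also depends on how finely VAS is recorded, and section 2.4 gives only the end anchors.

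**Conclusion.** The point holds and should be corrected: section 2.5 assigns its two tests the wrong way round. The primary VAS outcome and all other numeric outcomes are affected. Under the stated assumptions (1-point difference, SD 1.5 to 2.0, 50 per arm, two-sided 0.05), the named test has power of about 0.01 to 0.5, against about 0.7 to 0.9 for a t test. These figures illustrate scale and are not the trial's own design values. That the pairing is reversed needs no assumption, nor does the result that χ² cannot respond to treatment when all values are distinct. For yes/no complications the effect is negligible.

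**What to change.** Swap the two tests. Suitable wording: *Continuous outcomes (VAS, operative time, radiation exposure time, length of stay, ODI) are compared between arms with independent t tests; categorical outcomes (complications) are compared with χ² tests, or with Fisher's exact test where expected counts are small.* The sentence should not offer a choice between adjusted and unadjusted analysis, since that would open a new undefined option for the primary comparison. If a separate analysis plan exists, check that it uses the same pairing. The cost is one sentence of text, with no change to data collection, sample size or trial conduct.

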## Results

3

The clinical outcome variables between groups are shown in Table 1.

## Discussion

4

To the best of our knowledge, this is the first randomized controlled trial to assess the safety and effectiveness of bilateral IFB for PELD pain control. LDH is a common orthopedic disease and a worldwide health problem characterized by low-back and radiating pain.^[13,14]^ PTED has become one of the optimal clinical treatments for LDH due to the advantages of minimal invasion, less blood loss, and rapid recovery.^[15,16]^ Surgery and anesthesia are associated with a stress reaction, immunosuppression, and postoperative pain, which prolong hospital stays and increase the economic burden of patients.^[9]^ Appropriate anesthesia is important to achieve improved clinical outcomes.^[17]^ The lack of a definitive “gold standard” and various programs of anesthesia method during operation indicate that there is much room for improving the perioperative pain control. Recently, IFB is popular used in PELD. However, if conducted unilateral IFB only, satisfactory and instant distribution of local anesthetic to the opposite side usually could not be obtained, due to the mass effect of herniated nucleus pulposus, spinal stenosis, intraspinal adhesion, different puncture site and other factors. Therefore, bilateral IFB is recommend for intraoperative pain management in PELD. Considering that the sample size is small. Our findings must be replicated in more research centers and in larger samples, and evaluate over longer periods of follow-up, before final conclusions can be drawn.

## Conclusion

5

This investigation can offer a reliable basis for the effectiveness and safety of IFB in treating the PELD pain.

## Abbreviations

Abbreviations: IFB = intervertebral foramen block, LDH = lumbar disc herniation, ODI = Oswestry Disability Index, PELD = Percutaneous endoscopic lumbar discectomy.
